**5.5 Intervention**

All infants in the NICU eligible for the study will be assigned for bathing three times a week with washcloths impregnated with 2% chlorhexidine gluconate (Clinell ® Chlorhexidine wash cloths, GAMA healthcare) during the initial 6-months study period (intervention), followed by standard bathing during the second 6-months period, then again intervention period for 6 months and standard bathing for 6-months. Total study period- 2 years.

**Inclusion criteria**: infants weighing ≥1500 grams and ≥10 days of age; parents’ informed consent

**Exclusion criteria:** infants weighing <1500 grams or <10 days of age**;** parents’ refusal to sign informed consent.

For standard bathing procedure see appendix 1.

Before the study initiation, as well as at the beginning of each study period, nurses will be instructed on the proper technique for bathing patients. Bathing will be performed according to product brochure, three times a week.

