**5.9 Statistical analyses**

Changes in the rates of BSI and clinical sepsis will be compared between the intervention and the control period. Continuous variables will be examined with the use of two-sample t-tests and linear regression modeling, and categorical variables will be examined by means of Fisher’s exact test. Cox proportional-hazards regression model will be used to compare the time from admission until the first primary bloodstream infection , clinical sepsis or acquisition of MDRO between the control and intervention periods.

**Sample size calculation:** based on our ongoing surveillance, there are 2-3 BSI events per 1000 patients –days in our NICU. In order to detect a 50% reduction in BSI rates , we will need 37,096 patient days (18,548 in each group) in order to have 80% power to reject the null hypothesis, with 0.05 level of significance. Currently, our average annual census is 45,000 patient days. therefore, a 2-year study will have >80% power to reject the null hypothesis (the BSI rates in the control period equal the rates in the intervention period).

**For the preliminary study, we used the data in Milstone et al. ^18^ who reported no serious adverse skin reactions and an incidence of 1.2 minor skin reactions per 1000 patient days. A sample of 500 patient days will enable us to detect a ten-fold higher rate of minor skin reactions. Therefore at least 200 patient days in each group of the preliminary study (>600 patient days), would suffice.**

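### The 37,096 patient-days for 80% power leave no room for variation in the unit's BSI rate between the four 6-month blocks

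*Protocol*

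**What the plan says.** The sample size paragraph of protocol section 5.9 starts from the unit's surveillance, where "there are 2-3 BSI events per 1000 patients"-days. It sets the target, "In order to detect a 50% reduction in BSI rates", and arrives at "37,096 patient days (18,548 in each group) in order to have 80% power to reject the null hypothesis", "with 0.05 level of significance". It names neither the formula nor whether the test is one- or two-sided. From a census of 45,000 patient-days a year it then concludes that a two-year study has more than 80% power.

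Section 5.3 places the study in one NICU. Under section 5.5 all eligible infants receive chlorhexidine in the opening 6 months, "followed by standard bathing during the second 6-months period, then again intervention period for 6 months and standard bathing for 6-months". Each method therefore has two unit-wide blocks.

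Section 5.9 says that the rates of BSI and clinical sepsis will be compared between intervention and control periods. It lists t-tests, linear regression, Fisher's exact test and Cox regression. It mentions no variance between blocks, either for the power or for the rate comparison.

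**The concern.** The method changes only when the block changes. A shift in the unit's underlying rate from one block to another (an outbreak, staffing, case load) cannot be separated from the effect of bathing within that pair of blocks. Counting more patient-days reduces chance variation in the number of events, but it leaves this second source of variation untouched, because there are still only two blocks per method.

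A power figure based on event counts alone is therefore the best case. If the underlying rate moves at all between blocks, the power is lower. If the analysis also ignored that movement, an ordinary swing in the unit's rate could be read as an effect of chlorhexidine more often than the nominal 5%, and more often still as exposure grows.

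**Working it through.** **Inputs.** From section 5.9: baseline 2 to 3 BSI per 1000 patient-days, 50% reduction, 80% power, alpha 0.05, 18,548 days per group, census 45,000 a year (90,000 in two years, so 45,000 per group). From section 5.5: two blocks per method. Assumed: CV, the coefficient of variation of the true rate between blocks, shown at 0, 0.1 and 0.2.

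**1. The protocol's figure.** With Poisson variance only,

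n per group = (z_alpha + z_beta)² × (λ0 + λ1) / (λ0 − λ1)².

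For 2.0 versus 1.0 per 1000, one-sided 0.05:

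(1.645 + 0.842)² × 0.003 / 0.001² = 18,547.67, rounded up to 18,548, and twice that is 37,096.

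The match is to the last digit. Two-sided, the formula gives 23,547 at 2.0, 18,837 at 2.5 and 15,698 at 3.0 per 1000. The 2.5 value is close but not equal. No matching variant contains a between-block term.

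**2. Adding block variance.** With two blocks per method,

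Var = (λ0 + λ1)/n + (CV²/2)(λ0² + λ1²), and power = Φ[(λ0 − λ1)/√Var − z_alpha].

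The second term does not contain n. Example at n = 18,548 and CV 0.2, one-sided: Var = 1.617×10⁻⁷ + 0.02 × 5×10⁻⁶ = 2.617×10⁻⁷, SE = 5.116×10⁻⁴, and Φ(1.955 − 1.645) = 0.62.

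Power at 2.0 versus 1.0 per 1000, block variance treated as known:

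| CV | 18,548 per group, one-sided | 45,000 per group, one-sided | 45,000 per group, two-sided |
|---|---|---|---|
| 0 | 80% | 99% | 97% |
| 0.1 | 75% | 95% | 91% |
| 0.2 | 62% | 79% | 69% |

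On the one-sided inputs, 80% power needs 21,939 days per group at CV 0.1 and 48,587 at CV 0.2.

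**3. Type I error if only Poisson error is used.** This uses a different basis from the table: two-sided 5% test, 2.5 per 1000 in both groups. The Poisson variance is 2λ/n and the true variance is 2λ/n + CV²λ². The type I error is 2[1 − Φ(1.96k)], where k is the square root of the ratio of the first to the second.

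- 18,548 per group: about 8% at CV 0.1 and 16% at CV 0.2.
- 45,000 per group: about 12% at CV 0.1 and 28% at CV 0.2.

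**4. Does the 2 to 3 range give the CV?** Read as a uniform spread it gives (1/√12)/2.5 = 0.115; read as plus or minus one SD it gives 0.5/2.5 = 0.2. But a 6-month block at the stated census has 22,500 days and, at 2.5 per 1000, 56.25 expected events, so chance alone gives a CV of 1/√56.25 = 0.133. The range does not identify a true CV.

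**5. Estimating the variance from the four blocks alone.** Four blocks leave 2 degrees of freedom. A two-sided t comparison of log block rates, at 45,000 per group and 2.0 versus 1.0 per 1000, has power of about 53% at CV 0, 45% at 0.1 and 31% at 0.2.

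**The case against.** A reader might infer that the trial as planned lacks the power it states. The protocol does not support that in general. Its claim about the trial itself is the two-year one, and at 45,000 days per group power is still 91% to 95% at CV 0.1. It fails only near CV 0.2, and at 2.5 per 1000 with a one-sided test it is 82% even there (72% two-sided). This part of the objection stands. The slack does rest on the full census, while section 5.5 counts only consented infants of at least 1500 g and 10 days. With the synopsis's approximately 800 patients, 90,000 days would mean 112.5 days each.

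A reader might also take the range of 2 to 3 per 1000 as evidence that the rate really swings. As shown, chance alone could produce it, and the protocol does not say that it is a spread across periods. The CV stays an assumption.

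Finally, a reader might conclude that the planned analysis has an inflated false-positive rate. Section 5.9 names no Poisson rate test, and the details of the model may sit in an analysis plan that is not shown. The 8% to 28% figures are conditional on an analysis with Poisson error alone.

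These objections leave the sample size statement exposed. The protocol itself makes that statement, and its figure is reproduced exactly with no between-block variance.

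**Conclusion.** The concern holds for the stated 37,096 patient-days. On the inputs that reproduce the figure, any true variation between blocks brings power below 80%: 75% at CV 0.1 and 62% at CV 0.2. At a higher baseline there is some margin; for example, 2.5 per 1000 one-sided still gives 82% at CV 0.1. The two-year claim is conditional: it survives CV 0.1 and, on the 2.0 per 1000 inputs, fails at CV 0.2, provided that 45,000 days per group accrue. More patient-days do not remedy an analysis that ignores block variance; its type I error rises with exposure.

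The conclusion rests on three assumptions: the formula is inferred from the exact match, the CV range is assumed, and the power figures treat the block variance as known. If it had to be estimated from the four blocks alone, power would be much lower.

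**What to change.** 1. From the unit's past surveillance, estimate how much the BSI rate varies from one 6-month period to the next, after subtracting the Poisson variance expected from the event counts.
2. Restate the power in section 5.9 over a range of CV, for both 37,096 days and the exposure expected over two years, with the baseline rate and the sidedness of alpha given.
3. Compare BSI rates with a variance at block level. Options are a random block effect whose size is informed by the historical surveillance, or the block as the unit of analysis, noting that four blocks leave only 2 degrees of freedom.

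Two apparent remedies should be avoided. A fixed period effect is aliased with bathing, because each block has one method in one unit. Monthly overdispersion alone treats months in the same block as independent: in simulation at CV 0.2 it lowered type I error only from 16% to 13% at 18,548 days per group, and from 28% to 22% at 45,000.

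The work is a short recalculation on data that the unit already holds. The price is a less favourable stated power and wider intervals.

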**1. Study Synopsis**

| Protocol Title | Evaluation of the Effectiveness of Chlorhexidine Bathing in Reducing Nosocomial Infections in the Neonatal Intensive Care Unit |
| --- | --- |
| Protocol Number |  |
| Sponsor |  |
| Primary objective | To determine if daily bathing with chlorhexidine impregnated  washcloths will reduce the incidence of bloodstream infections within the neonatal intensive care unit (NICU) . |
| Study design | This is a prospective, controlled; crossover study of daily bathing with no-rinse, 2% CHG impregnated washcloths versus bathing with water/soap or water according to gestational age and weight (e.g. standard bathing). The trial will take place in the NICU.  **In the preliminary phase of the study we will establish the safety of chlorhexidine bathing using Clinell ® Chlorhexidine wash cloths on three groups of patients: term infants admitted to the NICU; late preterm infants (34-37 weeks); preterm infants 30-34 weeks of gestation. Interim analysis for adverse events will be performed after each group of patients.**  **In the subsequent phases of the study,** all infants admitted to the NICU and enrolled in the study will be bathed three times a week with Clinell ® Chlorhexidine wash cloths during the initial 6-months study period (intervention), followed by standard bathing during the second 6-months period, then again intervention period for 6 months and standard bathing for 6-months. Total study period- 2 years.  Data collection will include all bloodstream infections as well as surveillance cultures |
| Number of subjects | Approximately 800 patients in both arms  **Up to 60 patients (at least 200 patient days) in the preliminary study** |
| Study population | Infants **>=10** days ,weighing **>=1500** grams admitted to the NICU |
| Duration of participation | Duration of NICU stay OR for the duration of invasive hardware (e.g intravacular catheters, nasogastric tubes etc. ) |
| Treatment | Bathing three times a week with either:  a.2% chlorhexidine gluconate cloth  b. water/mild soap +water |
| Assessment of efficacy | The primary efficacy endpoint will be the reduction in bloodstream infections incidence during those study periods where the 2% Chlorhexidine Gluconate Cloth will be utilized.  Additional study endpoints include overall incidence of colonization with multi-drug resistant organisms (MDRO) and time to colonization |

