**TBD**

3. Background

Preterm delivery rates in developed countries, including Israel, vary between 5-11%^[[1]](#endnote-1),^^[[2]](#endnote-2)^. Nosocomial infections (NIs) are a major health problem among premature infants, and are associated with increased morbidity, mortality, length of hospital stay, and costs^[[3]](#endnote-3),^^[[4]](#endnote-4)^. Overall infection rates range from 8.9 to 62 infections per 1,000 patient days^[[5]](#endnote-5)^’^[[6]](#endnote-6)^. Over the last 25 years, the improvement in survival of premature infants was paralleled by an increased rate of nosocomial infections (NI), especially among very low birth weight (VLBW) infants, who develop NI in 21-43% of cases^3^. This incidence is inversely related to gestational age and birth weight and directly correlated with severity of illness, length of stay, ventilation, central catheters, parenteral nutrition days, and broad spectrum antibiotics.

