**4. Expected significance**

National data from the USA indicate that almost a quarter of very low birth weight infants will have one or more episodes of sepsis. Compared with infants without sepsis, infants with sepsis had a significantly longer hospital stay (79 vs.60 days), had a 2-fold increase in the number of days on mechanical ventilation, and had a significantly higher mortality rate (18% vs 7%)3. Another American study estimated that, on average, the cost of NICU care was $16,800 greater per infant who experienced NICU-associated BSI^[[32]](#endnote-32)^. Approximately 7% of infants, or >12,000 infants, are born prematurely in Israel every year^[[33]](#endnote-33)^. Extrapolating the American data to the Israeli NICU translates into a major health problem. The Ministry of Health and the Israel Neonatal Society have recently launched a national program aimed at minimizing the rate of NI in the Israeli NICUs^33^. In our NICU we have adopted this program and have increased staff education, active monitoring of compliance with guidelines, as well as adoption of the “search and isolate” policy, with twice a week screening of patients for colonization with MDRO.

Despite these measures, BSI rates remain high in our NICU, which prompt us to search for additional interventions such as CHG baths. The goal of the currently proposed study is to determine if universal use of a chlorhexidine based bathing system for patients in the NICU will decrease skin bacterial burden and lead to decreased horizontal transmission of MDRO.

Additionally, we hypothesize that reduced skin colonization with opportunistic bacterial

pathogens will result in a reduction in the rate of CLABSI, BSI and clinical sepsis in comparison to regular bathing procedures.

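### The claim of more than 80% power rests on the whole unit's patient-days, not those of eligible, consented infants, and is not reconciled with about 800 patients

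*Protocol*

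**What the plan says.** Protocol section 5.9 takes its base rate from local surveillance: "there are 2-3 BSI events per 1000 patients –days in our NICU". It sets the target ("In order to detect a 50% reduction in BSI rates") and arrives at 37,096 patient-days, 18,548 per group, for 80% power at a 0.05 level. It does not say whether the test is one- or two-sided, or which point of the 2-3 range was used. It then concludes: "Currently, our average annual census is 45,000 patient days. therefore, a 2-year study will have >80% power to reject the null hypothesis".

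Other sections decide who supplies patient-days:

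- Section 5.5 admits "infants weighing ≥1500 grams and ≥10 days of age", with parental consent, and excludes everyone else.
- Section 5.7 reviews cultures and antibiotic orders for study participants only.
- The Synopsis plans "Approximately 800 patients in both arms" and gives participation as "Duration of NICU stay OR for the duration of invasive hardware".

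Two background statements bear on the inputs. Section 3 says of nosocomial infection: "This incidence is inversely related to gestational age and birth weight". Section 4, citing US data on very-low-birth-weight infants, says "infants with sepsis had a significantly longer hospital stay (79 vs.60 days".

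**The concern.** The power conclusion follows directly from the census, and the census is the wrong denominator. Days lived below 1500 g, days before day 10 and all days of infants whose parents do not consent are in the 45,000 but cannot enter the analysis. The base rate has the same fault. It describes the whole unit, while the protocol itself says infection is more frequent in smaller and less mature infants, whose time is partly or wholly outside the study.

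The exposure is also never tied to the planned number of infants. If the eligible days fall well short, a null result could be read as evidence against an effect when the trial had limited ability to detect one.

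**Working it through.** **Inputs.** Control rate r1 of 2 to 3 per 1000 patient-days, rate ratio 0.5, 80% power, level 0.05, and a census of 45,000 days a year for 2 years (all section 5.9); 800 infants (Synopsis). The eligible share of the census, the consent rate and the eligible days per infant are not given, so they are shown as ranges.

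**Reproducing 18,548 per group.** For two Poisson rates, n per group = (z_α + z_0.80)² × (r1 + r2) / (r1 − r2)².

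- One-sided, 2 vs 1 per 1000: (1.645 + 0.842)² × 0.003 / 0.001² = 18,547.7, which rounds to 18,548; twice that is 37,096. This is an exact match.
- Two-sided, 2 vs 1 per 1000: (1.960 + 0.842)² × 0.003 / 0.001² = 23,547 per group, 47,093 in total.
- Two-sided, 2.5 vs 1.25 per 1000: 18,837. Close (1.6% higher), but not the stated figure.
- Two-sided, 3 vs 1.5 per 1000: 15,698.

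Among the two ends and the midpoint of the stated range, only the one-sided calculation at the low end gives the protocol's number exactly.

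**Share of the census needed.** Two years give 2 × 45,000 = 90,000 days.

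- Stated requirement: 37,096 / 90,000 = 41.2%.
- Two-sided at 2 per 1000: 47,093 / 90,000 = 52.3%.

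**Days per infant with 800 infants.**

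- Full census: 90,000 / 800 = 112.5.
- Stated requirement: 37,096 / 800 = 46.4.
- Two-sided at 2 per 1000: 47,093 / 800 = 58.9.

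The only lengths of stay in the protocol are 60 days (no sepsis) and 79 days (sepsis), for very-low-birth-weight infants. Both are whole stays. Counted from day 10, and assuming admission at birth, they leave at most 50 and 69 days before any time below 1500 g is removed.

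**Power for a halving of the rate.** With n days per group, power = Φ[(r1 − r2) / √((r1 + r2)/n) − z_α]. Example for 16,000 days in total at 2 per 1000: 0.001 / √(0.003/8,000) = 1.633. Power is then Φ(1.633 − 1.960) = 37% two-sided and Φ(1.633 − 1.645) = 50% one-sided.

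| Eligible days per infant | Total days (800 infants) | Two-sided, at 2 and 3 per 1000 | One-sided, at 2 and 3 per 1000 |
|---|---|---|---|
| 20 (assumed) | 16,000 | 37%, 52% | 50%, 64% |
| 30 (assumed) | 24,000 | 52%, 69% | 64%, 79% |
| 40 (assumed) | 32,000 | 64%, 81% | 75%, 88% |
| 46.4 (stated requirement) | 37,096 | 70%, 86% | 80%, 92% |
| 60 (assumed) | 48,000 | 81%, 93% | 88%, 97% |
| 112.5 (full census) | 90,000 | 97%, 99.7% | 99%, 99.9% |

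**The case against.** The census is 90,000 / 37,096 = 2.4 times the stated requirement, so the authors could afford heavy exclusion. If about 41% of census days were eligible and consented, the stated requirement would be met. This stands. A reader might infer that the trial has less than 80% power, or about half what is claimed; the documents do not show either, because they give neither the eligible share nor the days per infant. The low figures above rest on an assumed 20 to 30 days.

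The stay comparison is also limited. It is US data on a different population, and 46.4 days lies below 60; only the full-census figure of 112.5 exceeds the quoted stays. If 800 meant each arm (1,600 in total), the needs fall to 23.2 and 56.3 days per infant and the mismatch weakens. The eligibility and consent objection is untouched by that reading.

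A reader might also infer that 18,548 comes from the midpoint of 2.5 per 1000. That gives 18,837 two-sided, so the documents do not support it. Nor can the one-sided test be taken as the sponsor's declared choice: it is the exact match, but it is not stated.

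Three further limits are fair. The weight criterion can be read as current weight, so small infants may enter once they reach 1500 g. A lower BSI rate in eligible time is therefore plausible, but no passage quantifies it. The primary outcome in sections 5.2 and 5.6 includes clinical sepsis, whose extra events would raise power for the combined outcome; the protocol's calculation and the figures here concern BSI alone. Finally, the Synopsis wording on invasive hardware might shorten exposure, but section 5.7 works from admission and discharge dates, so nothing here relies on it.

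**Conclusion.** The concern holds as a lack of support for the stated power. Section 5.9 compares a requirement with a patient-day total that the entry criteria and consent do not allow the trial to use in full, and the result is not reconciled with about 800 infants.

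The claim depends on unstated conditions: at least 41% of census days eligible and consented (52% for a two-sided test at 2 per 1000), and, with 800 infants in total, an average of 46 eligible days each (59 for that two-sided test). The BSI rate in eligible time must also be no lower than the one assumed. Sidedness alone moves power at 37,096 days and 2 per 1000 from 80% to 70%.

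The arithmetic is firm on what the claim requires. The actual power remains unknown until the eligible days and their BSI rate are supplied.

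**What to change.** Rewrite the sample size paragraph of section 5.9 as follows:

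- From existing unit surveillance, extract the patient-days and BSI rate for infants meeting the weight and age criteria, and apply an expected consent rate.
- State the base rate and the sidedness used for the 18,548.
- Show power for the 50% reduction at 2 and at 3 per 1000, as well as at the rate found in eligible infants.
- Make the 800 infants, the expected eligible days per infant and the required patient-days agree, and say whether 800 is the total or per arm.
- Replace the claim of more than 80% with the resulting figure.

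The cost is one query of data already held and a revised paragraph. No extra enrolment is asked for. The drawback for the sponsor is that the stated power may be less favourable.

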A recent multicenter study examined the use of chlorhexidine-impregnated washcloths among adult patients at nine intensive care and bone marrow transplantation units. The chlorhexidine group had 23% lower rate of MDRO acquisition and a 28% lower rate of BSI compared with the control group ^13^. A systematic review of 15 studies, 9 of which were randomized controlled trials, provided support for the usefulness of CHG in a variety of healthcare settings including intensive care units, internal and surgical hospital wards ^[[20]](#endnote-20)^ .

Studies that examined the use of CHG in neonates were conducted mainly in developing countries and evaluated single whole body cleansing of the newborn immediately after birth, with or without maternal vaginal cleansing. CHG concentrations varied between 0.25% and 1%, and its use was associated with a reduction in neonatal mortality in high-mortality settings, but did not show benefit in low neonatal mortality settings^[[21]](#endnote-21)^’^[[22]](#endnote-22)^’^[[23]](#endnote-23)^’^[[24]](#endnote-24)^’^[[25]](#endnote-25)^’^[[26]](#endnote-26)^ . A large multicenter study in 10 pediatric intensive care units (PICUs) in the USA found that the incidence of bacteremia was 36% lower among patients receiving daily CHG bathing (3.28 per 1,000 days, 95%CI 2.27–4.58)) compared with patients receiving standard bathing practices (4.93 per 1,000 days, 95%CI 3.91–6.15 ). There were no serious study related adverse events^[[27]](#endnote-27)^.

Despite the fact that CHG was not approved by the US Food and Drug Administration for use in infants <2 months of age, it was used in large well-designed clinical trials on tens of thousands of neonates without reported serious adverse events^[[28]](#endnote-28)^’^[[29]](#endnote-29)^. Moreover, a recent survey in US NICUs found that the majority were using CHG, mainly for central venous catheter (CVC) site preparation and CVC maintenance ^[[30]](#endnote-30)^.

A recent study examined the effect of 2%CHG bathing on prevention of central-line associated bloodstream infection (CLABSI) in the NICU. Eligible infants were those with CVC weighing >1000 grams or those weighing <1000 grams after day 28 of life. Using a quasi-experimental study design the authors compared the rate of infection among infants before and after the intervention and demonstrated a decrease from 6 to 1.92/1000 CVC-days. No adverse events were reported^[[31]](#endnote-31)^.

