**5.4 Preliminary study**

**In order to establish safety , we will enroll infants admitted to the NICU to three successive treatment groups , as follows: the first group will include term infants admitted to the NICU (gestational age ≥37+6 and >7 days old), the second group will include near-term infants (gestational age > 34+0 to 36+6 weeks and >7 days old) and the third group will include premature infants (gestational age >30+0 to 33+6 and >=10 days old). We intend to enroll up to 20 patients in each group, for a minimum of 200 patient days per group (see sample size estimation). All infants will be assigned for bathing three times a week with washcloths impregnated with 2% chlorhexidine gluconate (Clinell ® Chlorhexidine wash cloths, GAMA healthcare) for the duration of their NICU stay. The infant’s skin will be monitored continuously as described below (see ‘6.0 Safety and monitoring’ and appendix 2). In case of grade 3 or 4 reactions, the study interventions will be temporarily suspended, and the adverse event will be reported to the Helsinky committee and to the study steering committee. If no grade 3 or 4 reactions will be encountered after at least 200 patient days per group, enrollment to the subsequent group will be performed (e.g if no grade 3-4 reaction will be encountered for 200 patient days in group 1, we will start enrolling patients for group 2 etc.). If no grade 3-4 dermatitis is encountered in the preliminary study, we will initiate enrollment as described below (‘5.5 intervention’)**

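### Preliminary phase: the sample-size argument covers pooled minor reactions, but each go-ahead rests on zero grade 3-4 reactions in 200 patient-days of one group, and the synopsis minimum conflicts

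*Protocol*

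**What the plan says.** Section 5.9 takes as its benchmark "an incidence of 1.2 minor skin reactions per 1000 patient days", credited to reference 18, and notes that the same source had no serious skin reactions. It continues: "A sample of 500 patient days will enable us to detect a ten-fold higher rate of minor skin reactions". From this it concludes: "Therefore at least 200 patient days in each group of the preliminary study (>600 patient days), would suffice".

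Section 5.4 describes how the days are used. Three groups are enrolled one after another: term, near-term, then infants of 30 to 33 completed weeks. "We intend to enroll up to 20 patients in each group, for a minimum of 200 patient days per group", it says, and refers to the sample size estimation for support. The step to the next group is conditional: "If no grade 3 or 4 reactions will be encountered after at least 200 patient days per group", the next one opens. The main study starts if no grade 3-4 dermatitis is seen in the preliminary study. Section 6.0 has grade 3 and 4 skin reactions reported as serious adverse events.

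The synopsis, under number of subjects, says: "Up to 60 patients (at least 200 patient days) in the preliminary study".

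**The concern.** Section 5.4 sends the reader to section 5.9 for the basis of the 200 days, and what section 5.9 offers does not match the decision in two respects.

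- **Unit.** The calculation is for 500 days, reached only by adding the three groups together. The decisions are taken in sequence, each on one group's 200 days, which is 40% of the 500. The groups differ in maturity, so a risk confined to the least mature infants is judged on that group's days alone.
- **Event.** The calculation is about minor reactions. The gate is about grade 3-4 reactions, for which the protocol gives no reference rate, target rate or error probability.

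The stated minimum exposure also differs three-fold between the synopsis and the body. And reference 18, cited for the benchmark, is listed as a national survey on MRSA colonisation in NICUs, an unlikely source for skin reaction rates under bathing.

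The phase is meant to establish safety before wider use. An ethics or steering committee reading section 5.9 would take more assurance from a clean group than 200 days can give.

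**Working it through.** **Inputs.** Benchmark 1.2 per 1000 patient-days, ten-fold alternative 12 per 1000, and exposures of 500, 200 per group and 600 pooled: all from section 5.9. Gate of zero grade 3-4 reactions: section 5.4. The alpha of 0.05 and power of 80% in section 5.9 belong to the bloodstream infection calculation. None is stated for this phase, so I assume a one-sided exact Poisson test against the fixed benchmark, at 0.05 or 0.025.

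**1. The plan's own figure, 500 days.** Expected events are 500 × 0.0012 = 0.6 and 500 × 0.012 = 6.
- P(≥3 | 0.6) = 1 − e^(−0.6)(1 + 0.6 + 0.18) = 0.023, so reject at 3 or more.
- Power = P(≥3 | 6) = 1 − e^(−6)(1 + 6 + 18) = 0.938.

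So 500 days are enough. The figure cannot be reproduced as a unique minimum without a stated alpha and power. The nearest variants (normal, square-root and exact Poisson, each at 95% power) give 478 to 525.

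**2. Pooled 600 days.** Expected events are 0.72 and 7.2. Power is 97.5% at one-sided 0.05 (reject at ≥3) and 92.8% at 0.025 (reject at ≥4). The pooled claim is sound.

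**3. One group, 200 days.** Expected events are 0.24 and 2.4.
- P(≥1 | 0.24) = 1 − e^(−0.24) = 0.213, too large for a rejection rule.
- P(≥2 | 0.24) = 1 − e^(−0.24)(1 + 0.24) = 0.025, so reject at 2 or more.
- Power = P(≥2 | 2.4) = 1 − e^(−2.4)(1 + 2.4) = 0.692. The exact binomial gives 0.693.

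At 200 days, 80% power needs about a 12.5-fold rise. For a ten-fold rise, 80% power is first reached at 250 days (one-sided 0.05) and holds for every larger exposure only from 357.

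**4. The event that drives the gate.** With zero events in T days, the one-sided 95% upper limit is −ln(0.05)/T = 2.996/T.

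| Days with zero grade 3-4 events | Upper limit per 1000 patient-days |
| --- | --- |
| 200 (one group) | 15.0 |
| 600 (all three) | 5.0 |

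The chance that a group passes is e^(−rate × 200). For illustration, with an assumed true rate of 5 per 1000 (no such rate is given in the protocol):
- one group passes with probability e^(−1) = 0.37;
- if the rate is the same in all three groups, all pass with probability e^(−3) = 0.05.

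**5. The minimum exposure.** Section 5.4: 3 × 200 = 600. Section 5.9: 200 per group, given there as more than 600. These agree. The synopsis attaches 200 to up to 60 patients, which is the full count of 3 × 20. As worded, it is 200 for the whole phase.

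**The case against.** The best defence is that section 5.9 makes a pooled claim, and the pooled claim is right. It never promises ten-fold detection within a group. That stands, and the point here is not an arithmetic slip. But section 5.4 relies on that estimate for decisions made per group and on another kind of event, so a correct pooled figure does not support them.

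The 69% depends on what detecting means. If one event counts, 200 days give 1 − e^(−2.4) = 91% at the ten-fold rate. At the benchmark rate, though, one event already occurs 21% of the time, so it does not show a rise. A normal approximation gives 78 to 81%, but is not valid with 0.24 expected events.

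The 200 days are a minimum: up to 20 infants per group are followed for their NICU stay, so actual exposure may be larger and the limits tighter. Monitoring also continues, with daily and twice-weekly skin examinations, serious event reporting and biweekly review. Both points stand and limit the consequence.

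Several stronger readings are tempting but not supported:
- **That sections 5.4 and 5.9 conflict.** They do not; only the synopsis differs.
- **That the shortfall is worse because baths are given three times a week against a daily-bathing benchmark.** This needs the 1.2 per 1000 to come from the paediatric daily-bathing trial (reference 27) and risk to scale with the number of baths. The protocol establishes neither.
- **That the gate would let a large number of severe reactions into the main phase**, found by applying 5 per 1000 to its intervention days. The 37% is for a single group. A uniform rate of that size passes all three groups only about 5% of the time. If it applies to one group alone, it cannot be spread over all main-phase days. Either way, reactions would not accumulate unobserved.

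**Conclusion.** The justification is wrong as written. It shows that pooled exposure can detect a ten-fold rise in minor reactions; it does not show that 200 days are enough for the decisions taken on them. For minor reactions, power within one group is about 69%, against 94% at the 500 days quoted. For grade 3-4 reactions, a clean group at the minimum exposure excludes only rates above about 15 per 1000 patient-days, and a clean phase of 600 days excludes rates above about 5 per 1000. The synopsis minimum is a third of that in sections 5.4 and 5.9.

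These figures assume a one-sided exact Poisson test, a benchmark taken as known, and independent patient-days. Clustering within at most 20 infants per group would reduce the information further. The grading form in Appendix 2 is not visible in the text at hand, so the split between minor and grade 3-4 reactions rests on section 6.0. The 1.2 per 1000 itself cannot be checked from the protocol; the citation is doubtful, and the figure need not be wrong.

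**What to change.** 1. In section 5.9, replace the sufficiency claim with what the exposure shows, naming the test. For minor reactions: about 69% power for a ten-fold rise in one 200-day group and 93 to 97% in the pooled 600 days (exact Poisson, one-sided 0.025 and 0.05). For grade 3-4 reactions: upper 95% limits of about 15 and 5 per 1000 patient-days after zero events.
2. Reconcile the minimum exposure in the synopsis with sections 5.4 and 5.9, so that all three give the same figure and say whether it is per group or in total.
3. Check and correct the reference given for the 1.2 per 1000 benchmark.
4. At the biweekly meetings already planned in section 5.8, report the cumulative grade 3-4 rate with its upper confidence limit, by gestational-age group, including during the main phase.

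The cost is some redrafting and one added table. The stated safety assurance becomes weaker, which is the honest position. No extra infants are needed and the clinical rule is unchanged.
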